### Data collection

All data will be recorded on standardised forms. On enrolment, demographic information (age, gender, ethnicity, household size, and so on), birth history, breast feeding history, prior illness and in utero and household smoke exposure will be recorded, and a physical examination will be performed by a study physician. The primary and secondary outcome measures (see below) are collected at the time points specified above. Serious and non-serious adverse effects (nausea, vomiting, diarrhoea, rash) will also be documented and monitored. Safety exit points are discussed in End points below.

### Specimen collection

At enrolment (baseline), all children will have a deep nasal swab (NS) specimen collected. In a subset, additional specimens will be collected at baseline and during exacerbations depending on feasibility (some children are unable to attend the study centre at the onset of the exacerbation) and willingness of parents to allow additional venipuncture. These specimens are:

A deep NS specimen for respiratory viruses, respiratory bacterial pathogens (with antibiotic susceptibility testing) and other potentially important respiratory pathogens (*M. pneumoniae, Chlamydia* spp) at baseline and at the beginning and resolution of an exacerbation. The technique used is identical to previous studies [34-36] where the specimens were described as nasopharyngeal swabs. The NSs are handled as per our research laboratory protocol (see below).

Bloods at baseline and at the beginning and end of each exacerbation for C-reactive protein (CRP), neutrophilic marker of inflammation (IL-6) [37], serum amyloid A (SAA) [33,38] and markers of viral infection (interferon gamma-inducible protein 10 (IP-10) and IL-10).

Sputum at baseline and at the beginning and end of each exacerbation (when possible) for lower airway microbiology and antibiotic sensitivity.

### Further description of scores and laboratory methods

#### Cough score

The verbal categorical descriptive score is a validated daily diary score of cough rated on a six-point scale (0 = no cough to 5 = severe cough and cannot perform activities) with increasing scores reflecting greater interference with usual activities. This rating was validated against an objective cough meter measure [31] and changes in cough scores have been shown to reflect changes in objective cough counts [39].

#### Parent Chronic Cough Quality of Life score

The Parent Chronic Cough Quality of Life (PC-QOL) is a 27-item questionnaire designed to assess the level of frequency of feelings (15 items) and worry (12 items) related to their child’s cough. It uses a seven-point Likert-type scale with higher scores reflecting less frequency and fewer worry concerns (that is, greater QOL) [40,41]. The minimal important difference is 0.62 determined by the distribution method and 0.9 determined by the anchor method [42].

#### Bacteriology of nasal swabs

Oropharyngeal sampling under estimates *Streptococcus pneumoniae* carriage by approximately 50% when compared with NS [43]. Thus, NS are the preferred method when evaluating the presence of antibiotic-resistant bacteria. Culturing, identifying and, when appropriate, serotyping common respiratory bacteria are established techniques at our research laboratory [36,44]. Swabs are stored in skim milk tryptone glucose glycerol broth medium at −80°C before being batch processed for typical respiratory bacterial pathogens, notably *Haemophilus influenzae (*including strains of non-typeable *H. influenzae)*, *Moraxella catarrhalis* and *S. pneumoniae*. Batches of swabs are thawed and 10-μL aliquots cultured overnight on selective media at 37°C in 5% carbon dioxide. Growth of *S. pneumoniae*, *H. influenzae* and *M. catarrhalis* is recorded and confirmed by standard techniques [36,45]. Four isolates each of *S. pneumoniae* and *H. influenzae* and two isolates of *M. catarrhalis* per positive swab are tested for antimicrobial resistance and stored [36,45]. *S. pneumoniae* isolates are serotyped using the Quellung method (antisera from Statens Serum Institute, Copenhagen,Denmark).

In addition to routine susceptibility testing using the calibrated dichotomous susceptibility disc diffusion method, azithromycin minimum inhibitory concentration (MIC) will be determined by Etests (AB Biodisk, Solna, Sweden) if the azithromycin disc annulus is <6 mm. For *S. pneumoniae*, the penicillin MIC is determined for penicillin non-susceptible isolates (oxacillin and/or penicillin disc annulus < 6 mm) and for *H. influenzae*, the ampicillin MIC is determined for isolates if the ampicillin disc annulus is < 6 mm. Interpretive criteria (Clinical and Laboratory Standards Institute breakpoints) used for *S. pneumoniae* are penicillin non-susceptible MIC > 0.12 μg/mL, azithromycin resistance MIC ≥ 2 μg/mL; and for *H. influenzae*, ampicillin resistance MIC ≥ 4 μg/mL, azithromycin resistance MIC > 4 μg/mL. A nitrocephin-based test will identify beta-lactamase activity in *H. influenzae* and *M. catarrhalis* isolates.

#### Assessment for viruses and atypical bacteria

We will use our previous methods [46,47]. Nucleic acids will be extracted from the media using the High Pure Viral Nucleic Acid kit (Roche Diagnostics, Sydney, New South Wales, Australia), according to the manufacturer’s instructions. Real-time polymerase chain reaction assays will be used to detect respiratory syncytial viruses (A and B), adenoviruses, influenza viruses (A and B), parainfluenza, human metapneumovirus, human coronaviruses (OC43, HK1, 229E, NL63), enteroviruses, rhinoviruses (and subtypes [48]) and the more recently described human viruses (human bocavirus 1, parechoviruses, human polyomaviruses K1 and WU) and *M. pneumoniae* and *Chlamydia* species [49].

#### Blood markers

Serum CRP (threshold 5 mg/L) are standard tests that will be analysed locally (diagnostic laboratory of each participating centre). SAA, IL-6 (threshold < 3 pg/mL), IL-10 (threshold < 0.5 pg/mL) and IP-10 (threshold 2.8 pg/mL) will be performed using ELISA commercial kits (R&D Systems, Minneapolis, MN, USA) at our research laboratory.

#### Spirometry

Spirometry (in children aged ≥ 5 years) will be performed using American Thoracic Society criteria and the FEV_1_% predicted recorded. We elected not to use oscillatory measures as we found no difference in airway resistance between steady and exacerbation states [33]. Thus we will use conventional spirometry although we do not expect to detect significant differences.

### End points

Participation is complete when the child’s clinical state returns to baseline and the ‘time to next exacerbation’ has been obtained. Other exit points are if the child is clinically worse prior to day 14 or intolerance to the trial medications requiring withdrawal from the study (as determined by the treating clinician).

### Outcome measures

#### Primary outcome

The primary outcome is the proportion of children whose exacerbations have resolved by day 14. Exacerbations will be considered resolved when symptoms and signs are the same as the baseline state. Children who are withdrawn from the study or receive additional antibiotic treatment will be categorised as non-resolved.

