### Intervention and follow-up

A double-dummy design is planned. If eligibility is fulfilled and after informed consent has been obtained, the child is randomised to one of three arms. At the start of the exacerbation, the child will receive amoxicillin-clavulanic acid with placebo-azithromycin, azithromycin with placebo-amoxicillin-clavulanic acid or placebo-azithromycin with placebo-amoxicillin-clavulanic acid. Amoxicillin-clavulanic acid dose is 22.5 mg/kg/dose (up to 40 kg) twice a day (max 900 mg/dose). Azithromycin dose is 5 mg/kg/day, max of 200 mg daily. Equivalent volumes in placebo will be given in all arms. All treatments will continue for 14 days.

An exacerbation is defined as an increase in sputum volume or purulence, or three or more days of change in cough (> 20% increase in cough score [31] or type (dry to wet) [32]). We validated this definition in our prospective study and found that the kappa values (between clinicians) of these symptoms and signs were excellent (> 0.75) [33]. Daily diaries will also be collected during exacerbations until the scores for two or more days reflect the child’s ‘baseline’ state, which for each child will be established at enrolment, prior to any exacerbations. This assessment consists of a combination of symptoms (daily cough (yes/no), cough quality (wet/dry/none) and cough score [31] averaged over two consecutive days) and signs (sputum colour (if any present) using a colour chart card (BronkoTest Ltd, London, UK), crackles on chest auscultation). Children will be reviewed on days 7 and 14 and at resolution of the exacerbation. The exacerbation is considered ‘resolved’ when symptoms and signs are the same as ‘baseline’ state. Post exacerbation, the children will be followed-up and clinically evaluated every three months for 18 months or until their next exacerbation. ‘Time to next exacerbation’ will be determined by the number of days from ‘resolution of current exacerbation’ to beginning of the next exacerbation.

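### The rule for resolution leaves out sputum volume, which alone can define an exacerbation, and does not say how a child who ends better than baseline is classified

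*Protocol article*

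**What the plan says.** All references are to the protocol article.

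- **Primary outcome** gives the rule for resolution: "Exacerbations will be considered resolved when symptoms and signs are the same as the baseline state". A child who is withdrawn or given additional antibiotics is non-resolved.
- **Intervention and follow-up** repeats the rule: "The exacerbation is considered ‘resolved’ when symptoms and signs are the same as ‘baseline’ state". Neither statement adds 'or better'.
- The same section gives the entry definition: "An exacerbation is defined as an increase in sputum volume or purulence, or three or more days of change in cough". The alternatives are joined by 'or', so increased volume is enough by itself.
- The same section lists what the baseline assessment covers. The symptoms are "symptoms (daily cough (yes/no), cough quality (wet/dry/none) and cough score [31] averaged over two consecutive days" and the signs are "signs (sputum colour (if any present) using a colour chart card (BronkoTest Ltd, London, UK), crackles on chest auscultation". Sputum volume is in neither list.
- Baseline is fixed once, "which for each child will be established at enrolment, prior to any exacerbations".
- **End points**, **Secondary clinical outcomes** and **Statistical analysis and reporting** speak more loosely of the child returning to baseline. The last of these counts such a child as resolved.
- **Sample size** plans 63 children per arm, 60% against 30% resolved, two-sided alpha 0.0245 and 84% power.

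**The concern.** Resolution by day 14 is the primary outcome, so the rule must classify every child the entry definition admits. It falls short in two ways.

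**Entry and resolution items do not match.** Increased purulence is answered by sputum colour, and a change in cough by cough score and cough quality. Increased volume has no counterpart. A child whose only change is volume equals baseline on every listed item from the start, and nothing in the list can register that the excess volume has persisted.

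**Equality with a chronic baseline.** The baseline list allows for daily cough, wet cough, coloured sputum and crackles before any exacerbation. A child with wet cough and crackles at enrolment, but a dry cough and clear chest on day 14, is not the same as baseline, although clinically the episode is over.

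The first fault adds successes that carry no information about treatment. The second, on its literal reading, removes true successes. Either would shrink the observed difference. Duration of exacerbation ends at resolution and time to next exacerbation starts there, so both inherit the same definition.

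**Working it through.** **1. Matching entry criteria to resolution items**

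| Entry criterion | Item in the baseline list |
|---|---|
| Increased sputum volume | none |
| Increased purulence | sputum colour |
| Change in cough score | two-day mean cough score, daily cough |
| Change in cough type | cough quality |

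Crackles are a resolution item without an entry counterpart, which does no harm here. Volume is the only entry criterion with no resolution item. Three other provisions could still catch a volume-only child: the override for withdrawal or additional antibiotics, exit as clinically worse, and the diary rule of two or more days at baseline. The first two catch only a child who triggers them. The diary is judged against the same baseline state, so it adds no volume check.

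**2. The two phrases side by side**

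'The same as' is used in Primary outcome and in Intervention and follow-up. 'Return to baseline' is used in End points, Secondary clinical outcomes, and Statistical analysis and reporting. A child better than baseline fails 'the same as' read literally and can pass 'return to baseline'. No section settles it.

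**3. Reproducing the stated power**

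Inputs from Sample size: n = 63 per arm, p1 = 0.60, p2 = 0.30, alpha = 0.0245 two-sided (z = 2.249). The continuity-corrected normal approximation, with m the mean of p1 and p2, is

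power = Φ{ [ (p1 − p2) − 1/n − z·√(2m(1 − m)/n) ] / √( [p1(1 − p1) + p2(1 − p2)]/n ) }

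= Φ{ [0.30 − 0.0159 − 2.249 × 0.0886] / 0.0845 } = Φ(1.003) = 84.2%.

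This agrees with the stated 84%; Fisher's exact test gives 84.5%. The sample size calculation is not in question.

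**4. Illustration: volume-only entries**

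Assume that 60% and 30% are the correctly classified rates, and that a share f of children in each arm enter on volume alone and are all counted as resolved. The observed rates are f + (1 − f) × 0.60 and f + (1 − f) × 0.30.

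| f | Active | Placebo | Difference | Power |
|---|---|---|---|---|
| 5% | 62.0% | 33.5% | 28.5 points | 79.1% |
| 10% | 64.0% | 37.0% | 27.0 points | 73.5% |
| 20% | 68.0% | 44.0% | 24.0 points | 61.5% |

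**5. Illustration: better than baseline counted as non-resolved**

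Assume that a share g of true resolvers, the same in both arms, is misclassified. The observed rates are 0.60 × (1 − g) and 0.30 × (1 − g).

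| g | Active | Placebo | Difference | Power |
|---|---|---|---|---|
| 5% | 57.0% | 28.5% | 28.5 points | 79.9% |
| 10% | 54.0% | 27.0% | 27.0 points | 75.3% |
| 20% | 48.0% | 24.0% | 24.0 points | 64.9% |

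The article gives neither f nor g. The tables show sensitivity and are not estimates.

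**The case against.** **No section states that improved children are failures.** The looser wording in three sections fits 'at least as good as baseline', and the categories named as non-resolved (withdrawn, additional antibiotics, clinically worse, dropped out) do not include a child who has improved. This stands. The equality wording is ambiguous and is not a proven source of misclassification. A reader might infer that such children will certainly be scored as failures; the article does not support that.

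**The volume fault is narrow.** It needs a child whose cough, sputum colour and crackles are all unchanged and who triggers no override. The article notes that sputum may be absent or unobtainable, so such entries may be uncommon. This stands as a limit on size. It does not remove the gap, because nothing else in the rule measures volume. Nor should such a child be described as resolved from day 0 without qualification: the outcome is judged by day 14, with reviews on days 7 and 14 and the overrides in force.

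**Bias against the antibiotics is not shown.** A reader might infer that improvement beyond baseline falls mainly on the active arms. That is plausible: the Discussion cites a small trial (13 children on roxithromycin) with reduced sputum purulence. But it concerned a different drug and reported nothing about finishing an exacerbation better than baseline. No section gives a rate by arm. Larger power losses can be produced by assuming unequal shares, but those shares would have no source.

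**The planned 60% and 30% may already refer to the outcome as defined.** Nothing shows that they assume another definition. This stands, so the tables do not show that the trial is underpowered.

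**This is a condensed article.** Item-level scoring may sit in a fuller document. But the article itself states the rule twice and lists the components, so what is at issue is a stated rule rather than an omitted detail.

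**Conclusion.** The point holds as a defect in how the primary outcome is specified. The mismatch over sputum volume follows directly from the text: the rule cannot detect persistent excess volume, and a child who enters on volume alone and triggers no override meets it regardless of treatment. The missing 'or better' is an ambiguity whose literal reading would fail some children who have recovered.

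The size is unknown. If 5% to 20% of children were affected equally in both arms, power would fall from 84% to between 79% and 62% through volume-only entry, or to between 80% and 65% through the equality wording. These figures rest on assumed shares and on taking 60% and 30% as correctly classified rates. They establish neither an underpowered trial nor a bias against either antibiotic. The change is still worth making, because the rule governs the primary outcome and two secondary outcomes and is cheap to repair.

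**What to change.** In Primary outcome and in Intervention and follow-up, define an exacerbation as resolved when every component is at or better than that child's baseline: cough score no higher, cough quality no wetter, sputum colour grade no higher, and no crackles beyond those present at baseline. Record sputum volume at baseline and in the exacerbation diary, with a category for no sputum, and require it to be no more than at baseline. Every entry criterion then has a resolution item. Use the same wording in Secondary clinical outcomes and in Statistical analysis and reporting.

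The cost is revised wording and one extra diary item, with no added visits or staff. Trial status reports that recruitment and randomisation have begun, so children already enrolled may have no recorded baseline volume. For those not yet in an exacerbation, it could be taken at the planned three-monthly review. The change should be made without sight of outcome data by arm.

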#### Secondary clinical outcomes

The main secondary outcome is the PC-QOL score. Other outcomes are the time to next exacerbation; requirement for hospitalisation; duration of exacerbation (persistence of symptoms till ‘return to baseline state’) and FEV_1_% predicted.

#### Secondary laboratory outcomes

Serum markers (CRP, SAA, IL-6, IL-10, IP-10) and data on viruses and respiratory bacterial pathogens, including antibiotic susceptibility patterns to penicillin and azithromycin, will be the secondary laboratory outcomes.

### Sample size

We plan to enrol 189 children (63 per arm), providing 84% power (α = 0.0245, two-sided) to detect a halving of the number of children in the active arm achieving resolution by day 14 (that is, azithromycin or amoxicillin-clavulanic acid: 60% resolved by day 14, compared with placebo: 30% resolved). This is a conservative estimate when compared with our prospective data of persistent symptoms in 24% of children based on the same diary card [50]. As the primary outcome will be obtained in all enrolled children, a drop-out has not been factored in for the intention-to-treat analysis. With 20% drop-out rate, data from 153 children (51 per arm) for ‘per protocol’ analysis provides a study power of 75%. Both treatment arms are compared with the same placebo arm. While the maximum efficiency is attained by allocating more children to the placebo arm (that is, using an allocation ratio of 1:1:√2), we chose to use a 1:1:1 allocation due to ethical concerns of deviating from standard care in respiratory centres.

In the main secondary outcome (PC-QOL), based on a between-group difference of 0.9 (minimum important difference [42]) (SD 0.9), our sample size provides power of 100% (α = 0.05) for data from at least 147 children (that is, assuming at least 80% retention of the 189 children enrolled). For secondary aim 2 (exploring factors that predict response to antibiotics), we will be examining eight main factors and thus a sample size of 147 exceeds the recommended minimum (n = 10 per factor) [51]. The eight factors are smoking, age, underlying aetiology, detection of virus (any versus none, then single versus multiple viruses), presence of azithromycin resistance and blood markers (IL-6, IL-10, IP-10 levels).

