### Statistical analysis and reporting

Data will be reported and presented in accordance with the updated CONSORT criteria [52]. Children will be analysed according to allocation status (regardless of subsequent management). An interim analysis is planned and a data safety and monitoring committee will determine if the study should be ceased should superiority of any antibiotic be identified after 50% of sample size is achieved.

For our primary aim, the main effects of the interventions will be determined by comparing the primary outcome (resolution of exacerbation) between groups ((azithromycin versus placebo) and (amoxicillin-clavulanic acid versus placebo)). Children who exit the study as clinically worse or drop-outs prior to the end point will be considered non-resolved. Those who exit the study as ‘returned to baseline’ will be considered resolved. Odds ratios will be calculated and, if appropriate, number needed to treat (for benefit) will be expressed. Tests of a treatment arm versus placebo at the end of the study for the primary outcome will be performed at the 2.45% significance level to account for spending some alpha at the interim analysis. Per protocol analysis will be an *a priori* secondary analysis.

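### The 84% intention-to-treat power holds only if no child drops out before day 14, or if the 60% and 30% rates already count drop-outs as non-resolved; the plan says neither, and its 75% per-protocol figure does not fit the second.

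*Protocol article*

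**What the plan says.** The Sample size section of the protocol article states: "We plan to enrol 189 children (63 per arm), providing 84% power", with "α = 0.0245, two-sided", for 60% resolved by day 14 on either antibiotic against 30% on placebo. It makes no allowance for loss: "As the primary outcome will be obtained in all enrolled children, a drop-out has not been factored in for the intention-to-treat analysis".

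Two other sections explain how every child comes to have an outcome. Under Primary outcome: "Children who are withdrawn from the study or receive additional antibiotic treatment will be categorised as non-resolved". Under Statistical analysis and reporting: "drop-outs prior to the end point will be considered non-resolved". The latter section also has children analysed as allocated and makes per protocol a secondary analysis.

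The Sample size section then turns to the per-protocol set: "With 20% drop-out rate, data from 153 children (51 per arm"), for which it gives 75% power. It states no new resolution rates for this smaller group. For the quality-of-life outcome it again refers to loss, "assuming at least 80% retention of the 189 children enrolled".

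**The concern.** Counting leavers as non-resolved is a legitimate way to complete the primary outcome, but it costs power. The rule protects the denominator and not the effect. If a fraction d of each arm leaves before day 14 and would otherwise have behaved like the rest, resolution rates p1 and p2 become p1(1 − d) and p2(1 − d), and the difference shrinks by the factor (1 − d). The plan reasons as if a complete denominator meant no loss.

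At stake is the headline power of the primary analysis. If it is overstated, the chance of missing a true effect of the planned size is larger than readers, funders and the monitoring committee are told, and a null result would be harder to interpret. The type I error and the analysis rule itself are not affected.

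**Working it through.** **Inputs, all from the Sample size section:** 63 per arm; two-sided alpha 0.0245; rates 60% and 30%; 20% drop-out with 51 per arm for per protocol; stated powers 84% and 75%. The non-resolved rule comes from Primary outcome and from Statistical analysis and reporting.

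**Method.** The plan names no test for the power calculation, so three were tried: exact enumeration of the two-sided Fisher test, the normal approximation with continuity correction, and the same approximation without correction. The corrected form is

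power = Φ[(|p1 − p2| − 1/n − z·s0) / s1],

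where z = 2.249 for alpha 0.0245, s0 = √(2p̄(1 − p̄)/n), s1 = √((p1(1 − p1) + p2(1 − p2))/n) and p̄ = (p1 + p2)/2. The uncorrected form omits 1/n.

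**Step 1: reproduce the 84%.** With n = 63 and 60%/30%, s0 = 0.0886 and s1 = 0.0845. Power = Φ[(0.30 − 0.0159 − 0.1994)/0.0845] = Φ(1.003) = 84.2%. Exact Fisher gives 84.5% and the uncorrected form 88.3%. The stated 84% is reproduced by a corrected or exact test with no drop-out.

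**Step 2: check the 75%.** With n = 51 and the same 60%/30%, the results are 73.4% (corrected), 72.8% (Fisher) and 79.8% (uncorrected). The stated 75% is close to the first two, so the plan evidently kept 60%/30% for the children who remain.

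**Step 3: apply the non-resolved rule, taking 60%/30% as completer rates.** n stays at 63 and each rate is multiplied by (1 − d).

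| Drop-out before day 14, each arm | Rates | Fisher | Corrected | Uncorrected |
|---|---|---|---|---|
| 0% | 60 / 30 | 84.5% | 84.2% | 88.3% |
| 5% | 57 / 28.5 | 80.2% | 79.9% | 84.8% |
| 10% | 54 / 27 | 75.4% | 75.3% | 80.8% |
| 15% | 51 / 25.5 | 70.4% | 70.2% | 76.5% |
| 20% | 48 / 24 | 65.5% | 64.9% | 71.8% |

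For the 20% row, corrected: s0 = 0.0855, s1 = 0.0828, and Φ[(0.24 − 0.0159 − 0.1924)/0.0828] = Φ(0.384) = 64.9%.

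**Step 4: the opposite reading, in which 60%/30% already count a 20% drop-out as non-resolved.** The 84% then stands, but the completer rates are 0.60/0.80 = 75% and 0.30/0.80 = 37.5%. With 51 per arm, s0 = 0.0982 and s1 = 0.0910, so power = Φ[(0.375 − 0.0196 − 0.2210)/0.0910] = Φ(1.48) = 93.0%. Exact Fisher gives 92.6%. That is about 93%, not 75%.

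**Step 5: compare.** With 20% drop-out before day 14, one reading gives about 66% for intention-to-treat and 73% per protocol. The other gives 84% and about 93%. Neither gives 84% with 75%.

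**Sensitivity to unequal drop-out (corrected form).** With 25% loss on active and 15% on placebo, power is 44%. With 15% on active and 25% on placebo, it is 82%.

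**The case against.** The strongest reply is that 60% and 30% are rates on the endpoint as defined, which already includes withdrawal and extra antibiotics as failures. On that reading 84% is right. This is possible, but the plan does not say so, and the per-protocol figure then has to change (Step 4). The reply moves the inconsistency from one figure to the other.

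The second reply has more force. A reader might infer that the trial's power simply is 66%, and that the risk of missing an effect is about twice what is stated (34.5% against 15.5% by Fisher). The documents do not support that as a fact about the plan:

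- The 20% is stated for the per-protocol set. It may include non-adherent children with an observed day-14 outcome, or loss after day 14. The retention statement treats 20% as a ceiling.
- The outcome window is only 14 days, with reviews on days 7 and 14.
- The End points section names clinical worsening before day 14 as an exit. Those children would be non-resolved anyway, so scoring them so costs nothing. If leavers would have resolved at half the average rate, 20% drop-out gives 60 − 0.2 × 30 = 54% and 30 − 0.2 × 15 = 27%, or about 75% power.
- Comparing 66% with the plan's 75% mixes calculations. Like for like, the pair is 66% and 73% by Fisher, or 72% and 80% uncorrected.

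Two further inferences should not be drawn. A reader might combine the drop-out rule with the End points section ("Participation is complete when the child’s clinical state returns to baseline", together with the time to next exacerbation) and conclude that a child who resolves on day 8 and leaves months later is scored non-resolved. The analysis section counts children who exit after returning to baseline as resolved, and the primary outcome is fixed at day 14, so this misclassification is not shown. A reader might also object that 153 and 147 are not both 80% of 189 (151.2). But 63 × 0.8 = 50.4 rounds up to 51 per arm, which gives 153, and 147 is offered as a minimum where stated power is 100%. Nothing turns on it.

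**Conclusion.** The point holds as an unstated condition on the headline power and an inconsistency between two figures in the same section. The 84% requires either no drop-out before day 14 or rates that already include drop-outs as non-resolved. The plan's stated reason, that the outcome is available for everyone, establishes neither.

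If 60%/30% are completer rates and drop-out is equal across arms and unrelated to outcome, intention-to-treat power is about 80%, 75% and 66% for 5%, 10% and 20% drop-out before day 14 (85%, 81% and 72% with an uncorrected test, whose starting value is 88%). The 66% is the low end of that range under equal drop-out, not the plan's expected power. Unequal drop-out could move the result either way. The 84% and 75% stand together only if essentially none of the 20% is loss that the rule would score as non-resolved.

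**What to change.** Choose one of two statements in the Sample size section and make both power figures follow from it.

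1. **60% and 30% are completer rates.** Replace the claim that drop-out need not be considered with intention-to-treat power over the drop-out expected before day 14: about 66% to 80% for 20% down to 5%, naming the test used. Say how much of the 20% is expected before day 14 and how much is non-adherence or later loss.
2. **60% and 30% already count drop-outs as non-resolved.** Say so, justify the rates on that basis, and recompute the per-protocol power with the higher completer rates (about 93% at 75% and 37.5% with 51 per arm, if all of the 20% leave before day 14).

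Either is a change of wording and needs no change to the analysis rule. The cost of the first is a less favourable stated power; the cost of the second is having to justify the rates. If the sponsor wished to keep 84% under the 20% scenario of the first option, the same corrected calculation needs about 91 per arm instead of 63.
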